## Methods

### Trial Design

The REHEAT RCT is designed as a 2-arm, parallel-group, multicenter randomized controlled trial (RCT). It involves voluntary home care workers—both employed and freelance—operating in the 2 study centers, 1 in Southern, Italian-speaking, and 1 in North-Eastern, German-speaking Switzerland, including 4 Swiss cantons (Figure 1). The Southern Switzerland study center, coordinated by the University of Applied Sciences and Arts of Southern Switzerland (SUPSI), comprises participants based in canton Ticino. The North-Eastern Switzerland study center is coordinated by the Zurich University of Applied Sciences (ZHAW), which also serves as the sponsor of the trial, and involves participants from the cantons of Zurich, Thurgau, and St. Gallen. The development of the RCT is also supported by the Swiss Tropical and Public Health Institute (Swiss TPH) as a project partner.

**Figure 1. fig1-00469580251405766:**
[figure not shown]
Flow diagram of the REHEAT RCT.

The RCT is implemented from June to September 2025, aligning with the period of highest likelihood for heatwave exposure in Switzerland. Participants in the treatment group receive the REHEAT strategy via a smartphone app, while those in the control group use the same app without active intervention features (only tracking of health- and well-being-related parameters) until the end of data collection in September 2025. Although the study is not blinded, all participants install the app during on-boarding activities, to reduce potential bias. To address the risk of contamination—given that participant from the treatment and control group may work together in the same team and share office spaces—participants are explicitly instructed not to discuss or share app content throughout the duration of the study.

This study design enables a robust estimation of the average treatment effect (ATE), as well as its heterogeneity across subgroups. The evaluation is supported by a longitudinal, multi-source, and multi-method data collection framework, which ensures comprehensive measurement of both outcomes and contextual factors over time. The ATE is estimated during the summer of 2025. In the event that no significant heat events occur during the planned study period, a contingency plan allows for an extension of the trial to the summer of 2026 (June-September 2026).

### Participants

Participants are primarily recruited through home care organizations in 2 Swiss regions: the Italian-speaking canton of Ticino in Southern Switzerland, and the German-speaking cantons of Zurich, Thurgau, and St. Gallen in North-Eastern Switzerland. Some of these organizations are public, others private home care providers. Additionally, cantonal institutions and cantonal or local home care associations support the recruitment effort by disseminating the invitation to self-employed workers.

The following inclusion criteria are applied:

Age 18 or older;Employed as a home care worker during the summer of 2025;Ability to continuously wear digital wearable device (smartwatch);Ownership of a compatible smartphone and willingness to install the REHEAT app.

The following exclusion criterion are applied:

Having an implanted pacemaker (as this is incompatible with data collection of heart rate variability);

Vulnerable populations (eg, older adults, pregnant workers) are not excluded, as they may benefit most from the intervention. Participation is voluntary, can be terminated by participants at any point without having to provide a reason. All participants are requested to provide written informed consent.

### Recruitment and Consent Procedures

Recruitment for the REHEAT study starts after the approval of the study through the ethical committee of the cantons of Zurich and Ticino on June 6th, 2025. Recruitment takes place through internal communication channels within partner home care organizations and through the presentation of the study among workers of these organizations by the REHEAT research team. Self-employed home care workers are contacted directly using cantonal public lists or through partner associations, while employed home care workers are reached via their employers’ official platforms, such as intranets, internal mailing lists, or presentations in team meetings. A brief announcement introducing the REHEAT study is shared with project representatives within each partner organization and tailored to the communication protocols and preferences of each organization. This message includes a link to the REHEAT webpage, inviting interested individuals to learn more about the study and how to participate.

The REHEAT webpage, available in English, German, and Italian, provides a comprehensive overview of the study, including its objectives, the reasons for focusing on home care workers, the expectations for their involvement, potential benefits, data usage, and detailed instructions for participation. The page clearly outlines the nature and purpose of the study, the procedures involved, its duration, as well as any potential risks, benefits, or discomforts. Clear information is also provided about data protection, including who will have access to personal data and how it will be processed and analyzed.

Contact information for the principal investigators at each study site is available on the REHEAT website, ensuring that all participants can ask questions before deciding to take part. The webpage also includes the study information sheet and privacy policy statement, enabling potential participants to make an informed consent. Participants are asked to download and review both documents, and then confirm—via an online form—their attendance at an in-person study presentation meeting with their designated principal investigator. During this meeting, participants can ask questions, raise any concerns, and decide whether to provide informed consent. If they choose to participate, on-boarding procedures follow. Participants are given at least 1 week to consider their decision before providing informed consent.

The study presentation meetings are conducted in person at the headquarters of each participating organization. During these meetings, the principal investigator and team members present the study, collect signed paper consent forms, distribute sealed, personalized envelopes containing an alphanumeric ID code and a digital wearable device (smartwatch of the company Garmin), and assist participants with the installation of the REHEAT app and the completion of the on-boarding process.

Once signed, paper consent forms are processed in accordance with data protection regulations and securely stored in both physical and digital archives located in Switzerland. Participants may withdraw from the study at any time by informing the research team via the procedure described in the information sheet. Upon withdrawal, the consent is manually deactivated, and any changes are logged in a dedicated electronic register.

As a sign of appreciation, all participants are offered the opportunity to keep the Garmin smartwatch at the end of the study (September 2025). The smartwatch, valuing approximately CHF 120, is provided unconditionally, regardless of compliance with the study’s procedures. The availability of this reward is clearly stated in all recruitment materials. Methodological research on the use of incentives in scientific studies indicates that unconditional incentives are more effective at increasing the participation rate than conditional incentives.^
43
^

### Randomization and Allocation

Randomization is carried out using a 1:1 allocation ratio through a computer-generated sequence, employing stratified block randomization to ensure balance between key co-variates.

Block randomization within strata works by first dividing participants into homogeneous subgroups (ie, strata) based on key baseline co-variates (eg, age). Within each stratum, participants are then randomized in small, fixed-size blocks to ensure that each treatment group is equally represented in every block. This dual-layered approach helps to maintain overall balance in treatment allocation across important co-variates (through stratification) while also preventing accidental imbalances due to random chance within each stratum (through blocking). It is particularly effective with a limited number of relevant predictors and in samples of small to moderate size, where simple randomization may lead to imbalance.^
44
^ In our case, we opted for stratification by age (<50 years vs ≥50 years), sex (male vs female), and geographical area (Southern vs North-Eastern Switzerland), and use blocks of 4 to ensure consistent treatment balance within each stratum.

The random allocation sequence is generated by the investigator overseeing the Ticino study site, without involvement from external personnel. Randomization is conducted after the completion of participant recruitment and immediately prior to onboarding and initiation of the intervention phase. Because randomization occurs only after recruitment is finalized, no ongoing allocation sequence requires concealment, eliminating the potential for selection bias due to prior knowledge of group assignments.

Participants in the treatment group receive the REHEAT heat adaptation strategy during Summer 2025 via the REHEAT app, installed on their smartphones. Participants in the control group gain access to the same content only after the summer, in September 2025. As noted previously, group allocation is not blinded. All participants install the study app during on-boarding (June or July 2025); however, only the treatment group has the intervention features activated from the start, while they remain inactive for the control group until the randomized controlled trial ends. Despite limited exposure, there remains some risk of contamination, as participants in both groups work within the same partner organizations and may interact regularly. To reduce this risk, all participants are clearly instructed not to discuss or share the content of the app with colleagues, a condition emphasized as essential to ensure the validity of the study.

### Intervention

The heat adaptation measures of the REHEAT strategy are co-developed by a multidisciplinary team of experts and stakeholders to tailor previously identified heat adaptation solutions to the specific needs and constraints of home care workers and their organizations. The intervention is designed to be low-burden, fully digital, and seamlessly integrated into daily routines.

The REHEAT app serves as the delivery platform, bringing the tailored measures directly to participants’ smartphones. For participants in the treatment group, the app provides enriched content from initial on-boarding, including practical guides on self-monitoring, hydration, nutrition, clothing and rest, and providing home care workers with app content reminder notifications (once per week), timely heat protection alerts (from 2 days before the heatwave), and local resource maps (Figure 2). In total, the REHEAT strategy covers 4 intervention domains with 12 heat adaptation features.

Personal Care (6 features). This domain focuses on individual well-being and includes a smartphone-based tool for tracking personal well-being, training materials on recognizing and managing heat-related symptoms, and reminders to check physiological data regularly. It offers expert advice on nutrition and hydration during hot weather, complemented with recipes and reminders of hydration, as well as tips and notifications aimed at improving sleep quality under heat stress.Heat Protection at Work (3 features). This domain provides practical guidance to help workers protect themselves from heat exposure on the job. It includes recommendations for sun protection (sunscreen, sunglasses, hats), advice on selecting and using cooling devices tailored to personal needs, and best practices for managing work clothing, preparing spare garments, and reducing heat exposure in vehicles and air-conditioned environments.Work Activity Planning (1 feature). This domain features a weather alert system integrated in the app, delivering push notifications with heat warnings and standardized advice (eg, “Tomorrow is expected to be hot; plan your breaks and bring sufficient water and fruit”). Unlike other services, these alerts will appear even if the app is closed or running in the background.Refreshment and Leisure Time (2 features). These domains improve access to local resources for breaks at work and for leisure. An interactive, geo-located map highlights designated rest areas such as parks, cafes, shops, and libraries that offer sanitary facilities or access to potable water. Additional alerts provide information on nearby leisure facilities such as swimming pools and gyms, including opening hours and special offers through local partnerships.

**Figure 2. fig2-00469580251405766:**
[figure not shown]
Features of the REHEAT app activated for the treatment group and the control group.

### Data Collection Procedures

The impact of the REHEAT strategy is evaluated using data collected from June to September 2025 through a multi-source, multi-method data collection system integrated into the REHEAT app. The multi-source approach involves gathering data from various sources—including physiological parameters, self-reports, and environmental data—while the multi-method component includes passive data collection via portable sensors installed in Garmin smartwatches, online surveys and tests.

As shown in Figure 1, participants complete a pre-intervention on-boarding questionnaire (June 2025) that assesses their general quality of sleep, mental health, and physical health. This questionnaire also includes items on participants’ sociodemographic characteristics and prior work experience, with a particular focus on years of service, prior training, and personal heat mitigation coping strategies. The same instrument is administered again at the end of the trial (September 2025) as part of the off-boarding procedure to estimate the overall impact of the REHEAT strategy, calculated as the change in these outcomes over time between the treatment and control groups.

Data on participants’ strain accumulation and daily sleep are collected “passively” throughout the study via Garmin smartwatches. Cognitive performance, emotional distress, and night recovery are collected throughout the study via the REHEAT app, using short closed-ended questionnaires (“diaries”) and tests.

The off-boarding questionnaire issued toward the end of the RCT includes questions on health and well-being. It also encompasses a treatment-group-specific section assessing participants’ practical application of the app contents and their evaluation of its usefulness, with particular attention to their prior experience and competencies in managing heat. In addition, the off-boarding questionnaire includes targeted items to assess the risk of contamination among control group participants and to support potential adjustments for any under- or over-estimation of the effects of the REHEAT strategy.

Finally, the off-boarding questionnaire for the treatement group includes closed- and open-ended questions to assess participants’ experiences and satisfaction with the REHEAT strategy. The evaluation of the REHEAT strategy will be also supplemented by qualitative interviews with a small sub-sample (Autumn 2025).

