### Statistical Analysis Plan

The evaluation of the REHEAT heat adaptation strategy consider the following 4 areas: implementation and compliance, impact, heterogeneity, and satisfaction.

Implementation and compliance: descriptive statistics and inferential comparisons assess baseline equivalence between treatment and control group and participant compliance across relevant sociodemographic characteristics, work experience, health condition, and selected outcomes. App usage data is analyzed using frequency distributions and stratified analyses by age, sex, and location to ascertain user engagement with the app.Impact Analysis: The impact of the REHEAT strategy is first evaluated using an Intention-To-Treat (ITT) approach, which yields the most reliable estimates for real-world interventions by preserving the benefits of randomization. In parallel, Local Average Treatment Effects (LATE) are estimated to assess the intervention’s effects at varying levels of participants’ potential heat exposure and compliance. ITT analyses are conducted at the individual level. The effects of REHEAT on the primary outcomes—measured at on-boarding and off-boarding—as well as on those monitored throughout the summer, are estimated using random-intercept mixed-effects models. By accounting for within-subject correlations over time, this approach supports a robust analysis of longitudinal data. LATE estimates on primary outcomes are derived using instrumental variable generalized linear mixed models (IV-GLMM), with MeteoSwiss weather data and REHEAT app usage serving as instruments. Specifically, passively recorded data on the frequency of use of the app’s features over time are used as a proxy for participants’ compliance with the intervention. These models control for randomization strata and blocks, as well as a set of time-invariant and time-varying co-variates deemed theoretically or empirically relevant. Because heat effects vary across time, cumulative exposure, and acclimatization,^57,58^ temporal factors are explicitly controlled in the analyses. Exposure to heat is modeled using distributed lag models to capture both immediate and delayed effects of temperature and humidex across pre-specified lag periods. Mixed-effects models include calendar-week splines, random slopes for time, and adjustments for survey date and recent mean temperature to account for differences in measurement timing and seasonal acclimatization.^
59

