^ Potential time-invariant characteristics of the respondents (eg, years of experience in home care, chronic conditions), and time-varying confounding due to intermediate variables (eg, workload changes, night shifts) are also addressed in sensitivity analyses.

Effect Heterogeneity: interaction terms are included in multilevel models to explore differences in outcomes by sex, age, geographical region, and time-related factors. Separate models assess moderation effects by these variables in both ITT and LATE frameworks. Random intercept multilevel regression techniques are used to model hierarchical longitudinal data that violate the independence assumption (ie, repeatedly measured continuous outcomes). The heterogeneity of heat episode effects are estimated by multiple-interaction models in which interaction terms between the heat episode, the participant’s area of work, age, and sex are estimated. To capture temporal heterogeneity, additional interaction terms assess whether the REHEAT strategy differentially mitigates heat effects over the course of the summer. Treatment-by-time interactions, such as calendar week, cumulative heat exposure, or time since onboarding, are used to examine whether intervention effects vary due to seasonal acclimatization or repeated exposure.^
59
^ Flexible calendar-week splines and random slopes for time allow for individual adaptation trajectories and evolving heat vulnerability. These analyses determine whether the REHEAT strategy effectively addresses the diverse and changing needs of home care workers operating in different areas of Switzerland, who are exposed to different climatic, organizational and contextual conditions, while also estimating average conditional treatment effects across demographic and temporal dimensions.

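### Questionnaire outcomes are to be compared as change from on-boarding; adjusting for the on-boarding value is equally unbiased and more precise, and the ITT covariate list should be closed

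*Protocol article*

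**What the plan says.** Under Data Collection Procedures, the on-boarding questionnaire "assesses their general quality of sleep, mental health, and physical health", and the same instrument is repeated in September 2025 "to estimate the overall impact of the REHEAT strategy, calculated as the change in these outcomes over time between the treatment and control groups". These measures belong to primary outcome domains in Table 1.

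The Statistical Analysis Plan section says that ITT effects on these outcomes, and on those followed through the summer, "are estimated using random-intercept mixed-effects models". It does not say how the on-boarding value enters. The LATE models (IV-GLMM) are described next, followed by: "These models control for randomization strata and blocks, as well as a set of time-invariant and time-varying co-variates deemed theoretically or empirically relevant". For the mixed-effects models the section then lists calendar-week splines, random slopes for time, and "adjustments for survey date and recent mean temperature to account for differences in measurement timing and seasonal acclimatization". The on-boarding value of the outcome is not named as a covariate anywhere.

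The same section adds that "time-varying confounding due to intermediate variables (eg, workload changes, night shifts) are also addressed in sensitivity analyses".

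**The concern.** Two features of the adjustment deserve attention.

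First, subtracting the baseline fixes its coefficient at 1, whereas the best coefficient is usually smaller. The stated calculation therefore carries avoidable noise from the on-boarding measurement. What is at stake is precision on the pre/post questionnaire outcomes.

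Second, the models may take in time-varying covariates without any limit to variables that treatment cannot affect. If the ITT models are included, a covariate measured after the app features are switched on could be a consequence of treatment, and conditioning on it would no longer give the total effect of assignment. The term confounding adds to the doubt: for the comparison of randomised arms, a variable arising after randomisation may be a mediator but does not confound assignment.

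**Working it through.** **Inputs.** From the protocol: 350 enrolled, 1:1 allocation (175 per arm), two-sided alpha 0.05, 80% power, stated total of 330 to 370, margin of about 10%. Not given: sigma, Delta, and the correlation rho between on-boarding and off-boarding scores. Rho is therefore varied as an assumption.

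**The plan's own figure.** The base sample size cannot be reproduced without sigma and Delta. The step from 330 to 370 is consistent with a 10% margin: 330/0.90 = 367 and 330 × 1.10 = 363. Solving the protocol's formula backwards for 330 in total gives a standardised effect of sqrt(2 × (1.960 + 0.842)² / 165) = 0.308. This serves below only as an illustrative effect. It relates to body-battery recovery, not to the questionnaires.

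**Variance per participant, SD 1 at both visits.**
- Change score: 2(1 − rho)
- Adjusted for baseline (ANCOVA): 1 − rho²
- Ratio, adjusted to change: (1 − rho)(1 + rho) / [2(1 − rho)] = (1 + rho)/2

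| Assumed rho | Change | Adjusted | Ratio | Fall in SE, 1 − sqrt(ratio) | 350 adjusted equals, with change scores (350/ratio) |
|---|---|---|---|---|---|
| 0.3 | 1.40 | 0.91 | 0.65 | 19% | 538 |
| 0.5 | 1.00 | 0.75 | 0.75 | 13% | 467 |
| 0.7 | 0.60 | 0.51 | 0.85 | 8% | 412 |

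Below rho = 0.5 the change score has variance above 1, so it is noisier than comparing off-boarding values alone.

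**Unequal variances.** With SDs s0 at on-boarding and s1 at off-boarding, the change-score variance minus the adjusted variance is s0² + s1² − 2·rho·s0·s1 − s1²(1 − rho²) = (s0 − rho·s1)². This is never negative, so the direction does not depend on the equal-variance assumption. The only cost of adjustment is one degree of freedom.

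**Does the mixed model already solve this?** In simulated trials of 350 participants (120 replicates each at rho 0.3 and 0.5), a random-intercept model with free baseline arm means gave the change-score estimate to within 1e-14. The empirical SE was 0.129 for change and 0.104 for ANCOVA or a common baseline mean at rho 0.3, and 0.098 against 0.084 at rho 0.5. All methods had essentially the same mean estimate, so the difference is precision and not bias.

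**Power at the illustrative effect of 0.308, 350 analysed.**

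| Assumed rho | Change | Adjusted | Total N for 80%: change / adjusted |
|---|---|---|---|
| 0.3 | 68.4% | 85.6% | 464 / 302 |
| 0.5 | 82.3% | 91.5% | 332 / 248 |
| 0.7 | 96.1% | 98.1% | 200 / 170 |

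**Covariates.** The sentence allowing "a set of time-invariant and time-varying co-variates deemed theoretically or empirically relevant" comes straight after the LATE description, so its reach to the ITT models cannot be settled from the text. The adjustments named specifically for the mixed-effects models are weather and calendar terms, which raise no difficulty. Workload changes and night shifts appear only under sensitivity analyses.

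**The case against.** The strongest reply is that the word change stands in a descriptive sentence about data collection, that the analysis section specifies mixed models, and that a mixed model with a common baseline mean is as efficient as ANCOVA. An unseen analysis plan may say so. This narrows the point but does not remove it. The one sentence that states how the effect is calculated names a difference in change, and nothing in the article points to a common baseline mean or baseline adjustment. It is also fair that only the pre/post questionnaire measures are affected, and that at rho 0.5 to 0.7 the change score still exceeds 80% power for the illustrative effect.

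A reader might infer more: that workload and night shifts are adjusted for in the main ITT model, so that the protection of randomisation is lost. The document does not support that, because it confines these variables to sensitivity analyses. Nor does it show that they are mediators. The Work Activity Planning domain is a single weather alert with standard advice, and nothing in it is said to alter workload or shifts. Coping behaviour is not named as an adjustment variable either. Any figure for a diluted effect would need a mediated share that the protocol does not give. Finally, heat exposure and compliance are not randomised, so confounding can be the right word in analyses of those; the objection to it applies only to the comparison of arms.

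**Conclusion.** The point holds as an improvement at no cost, not as an error that invalidates the analysis. The stated difference in change is unbiased under randomisation, but it is less precise than conditioning on a baseline that is already collected. The gain in SE is about 19%, 13% or 8% at rho 0.3, 0.5 or 0.7. These sizes rest on assumed correlations and equal variances; the direction does not. They also assume that the on-boarding questionnaire is completed before the app features become active, as its description as pre-intervention implies.

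The secondary point is one of clarity. The list of time-varying covariates is open, and whether it governs the ITT models is unclear. No size can be put on this from the document.

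**What to change.** 1. State that the ITT effect on each on-/off-boarding outcome is estimated from the off-boarding value, with the on-boarding value and the three stratification factors (age group, sex, region) as covariates. Equivalently, specify a mixed model with a common baseline mean for both arms. Align the sentence under Data Collection Procedures with this.
2. State which models the covariate sentence governs. For ITT, limit covariates to the randomisation strata, variables measured before the app features are activated, and exogenous weather and calendar terms. Timing relative to activation is the useful criterion, because randomisation takes place immediately before on-boarding.
3. Keep workload changes and night shifts in sensitivity analyses. For the arm contrast, label those models exploratory and describe the variables as possible mediators.

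The cost is wording in the analysis plan. All variables are already collected, and the protocol reports that no outcome data had been accessed at submission. If analysis has since begun, the change and its date should be recorded.
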